## Abstract

**Introduction:**

Ex vivo normothermic perfusion (EVNP) is a novel technique that reconditions the kidney and restores renal function prior to transplantation. Phase I data from a series of EVNP in extended criteria donor kidneys have established the safety and feasibility of the technique in clinical practice.

**Methods and analysis:**

This is a UK-based phase II multicentre randomised controlled trial to assess the efficacy of EVNP compared with the conventional static cold storage technique in donation after circulatory death (DCD) kidney transplantation. 400 patients receiving a kidney from a DCD donor (categories III and IV, controlled) will be recruited into the study. On arrival at the transplant centre, kidneys will be randomised to receive either EVNP (n=200) or remain in static cold storage (n=200). Kidneys undergoing EVNP will be perfused with an oxygenated packed red cell solution at near body temperature for 60 min prior to transplantation. The primary outcome measure will be determined by rates of delayed graft function (DGF) defined as the need for dialysis in the first week post-transplant. Secondary outcome measures include incidences of primary non-function, the duration of DGF, functional DGF defined as <10% fall in serum creatinine for 3 consecutive days in the first week post-transplant, creatinine reduction ratio days 2 and 5, length of hospital stay, rates of biopsy-proven acute rejection, serum creatinine and estimated glomerular filtration rate at 1, 3, 6 and 12 months post-transplant and patient and allograft survival. The EVNP assessment score will be recorded and the level of fibrosis and inflammation will also be measured using tissue, blood and urine samples. Ethics and dissemination. The study has been approved by the National Health Service (NHS) Health Research Authority Research Ethics Committee. The results are expected to be published in 2020.

**Trial registration number:**

ISRCTN15821205; Pre-results.

Strengths and limitations of this studyThis is a large multicentre randomised controlled trial. It will provide evidence of the effect of ex vivo normothermic perfusion (EVNP) on early graft function in donation after circulatory death kidney transplantation.The secondary objectives will allow us to examine the impact of EVNP on rates of acute rejection and longer term graft function and survival.Tissue, blood and urine samples will enable a more in-depth analysis of the effects of EVNP on ischaemia reperfusion.The limitation of this study is the lack of blinding. Owing to the nature of the technique and in order to report safety outcomes, it is not possible to blind the surgical team to the allocation of the kidney.Delayed graft function, defined as dialysis within the first week of transplantation, is subjective. However, it is the best accepted measure of early graft function.

## Introduction

Kidney transplantation continues to be limited by a shortage of organ donors. In response to this, there has been an increase in the use of kidneys from marginal donors and a significant proportion of transplant kidneys are now provided by donation after circulatory death (DCD) donors.^1^ DCD kidneys inevitably sustain a warm ischaemic insult prior to retrieval and 50–60% of these kidneys have delayed graft function (DGF) after transplantation.^1^ DGF is associated with an increased risk of acute rejection, longer in-patient stay and therefore greater cost, and may also reduce allograft survival.^1–7^ Moreover, when compared with standard criteria donors, DCD kidneys are three times more likely to be declined for transplantation due to concerns over their quality.^8^
^9^

Organ preservation has traditionally relied on hypothermic techniques based on the principle that refrigeration reduces cellular metabolism and tissue oxygen requirements. The problem is that in the anoxic hypothermic environment anaerobic cellular respiration continues, albeit at a slow pace. Oxidative phosphorylation is uncoupled and mitochondrial ATP production by chemiosmosis ceases.^10^ ATP continues to be generated at a much slower rate by substrate-based phosphorylation in the glycolytic pathway. This leads to depletion of intracellular ATP stores. Anaerobic respiration generates lactic acid leading to worsening intracellular acidosis and eventually loss of cell viability.^10^ The initial warm ischaemic injury sustained by DCD kidneys makes them less tolerant of cold ischaemic injury during hypothermic preservation.^11^
^12^

Normothermic perfusion techniques offer an alternative form of organ preservation and resuscitation that has the potential to limit some of the effects of hypothermic preservation techniques.^13^ Ex vivo normothermic perfusion (EVNP) is a novel technique that may help to recondition ischaemically injured kidneys prior to transplantation.^13^ The aim of EVNP is to restore metabolism and function to the kidney prior to transplantation by circulating a warm oxygenated red cell-based solution through the kidney.

EVNP has recently been introduced into clinical practice for kidneys from marginal donors.^13–17^ The early experience of renal transplantation after EVNP shows that the technique is feasible, safe and may improve early graft function.

This study will investigate the effect of 60 min EVNP in kidneys from DCD donors compared with the traditional technique of static cold storage.

The primary outcome measure will be DGF defined as the need for dialysis in the first 7 days post-transplantation. Secondary outcome measures will include more sensitive measures of renal function over the first 7 days post-transplant, length of hospital stay, graft and patient survival at 1 year and rates of acute rejection. Fibrosis, inflammatory markers and urinary biomarkers will also be examined in tissue, blood and urine.

## Methods

### Study type

A randomised controlled, open-label trial of the effect of EVNP on initial graft function in DCD kidney transplant. Figure 1 summarises the design of the trial.

**Figure 1 BMJOPEN2016012237F1:**
[figure not shown]
Trial design. CS, cold storage; DCD, donation after circulatory death; DGF, delayed graft function; eCRF, electronic case report form; eGFR, estimated glomerular filtration rate; fDGF, functional DGF; EVNP, ex vivo normothermic perfusion.

### Eligibility

Patients will be eligible for the trial if they meet the following criteria: patients undergoing a DCD kidney transplantation (Maastricht categories III and IV); the donor and recipient must be ≥18 years and it must be the patient's first or second kidney transplant.

Written informed consent will be taken from all patients included in the trial by a qualified member of the study team. Patients will not be eligible if the donor or recipient is under the age of 18 years, the DCD donor is in Maastricht categories I and II, patients receiving a third or subsequent kidney transplant, patients receiving multiorgan transplants, for example, simultaneous pancreas–kidney transplantation, patients receiving dual kidney transplants, paediatric en-bloc kidney transplants or kidneys that have been preserved by hypothermic machine perfusion. There will be four participating centres in the UK: Cambridge (lead), Newcastle, Guy's and Edinburgh.

### Randomisation

Patients will be allocated at random in a 1:1 ratio to either static cold storage (CS) plus 1 hour of EVNP (n=200) or CS (n=200) only. A patient information sheet will be given to potential recruits on admission for DCD kidney transplantation and written informed consent will then be obtained (see online supplementary appendices 1 and 2). Randomisation will be performed after the transplant recipient and kidney have both arrived in the transplanting centre and a final decision to proceed with transplantation has been made by a member of the study team. The randomisation will be performed on a web-based system (sealed envelope) which uses a computer-generated randomisation sequence. In cases where paired kidneys from the same donor are transplanted in the same centre, one kidney from the pair will be randomly allocated to CS and the other to EVNP. In these cases, the randomisation will also determine which kidney (right or left) will be transplanted first. Owing to the nature of the trial, no one is blinded to treatment allocation.

10.1136/bmjopen-2016-012237.supp1supplementary appendix

10.1136/bmjopen-2016-012237.supp2supplementary appendix

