#### Secondary outcome measures

The secondary outcome measures include incidences of primary non-function (PNF) defined as the permanent lack of allograft function from the time of transplantation (This will include graft losses due to irreversible rejection and vascular thrombosis. The cause of graft loss will be recorded.); the duration of DGF in days; functional DGF (fDGF) defined as <10% fall in serum creatinine for 3 consecutive days in the first week post-transplant; creatinine reduction ratio day 2 (CRR2=creatinine day 1−creatinine day 2/creatinine day 1) and CRR5 (CRR5=pretransplant creatinine−creatinine day 5/pretransplant creatinine);^19^ length of hospital stay, rates of biopsy-proven acute rejection rate and measures of renal function (serum creatinine and estimated glomerular filtration rate (eGFR)) at 1, 3, 6 and 12 months post-transplant. Patient survival (time from transplant to death) and allograft survival (time from transplant to graft loss or return to dialysis) will be recorded. The EVNP score will be calculated for each kidney undergoing EVNP (table 1). The predictive value of this assessment score on graft function and outcome will be evaluated. A clinical decision on the suitability of the kidney for transplantation will be made using normal criteria prior to perfusion. However, the EVNP assessment score will be taken into consideration. Arterial and venous samples will be collected during perfusion and used to measure oxygen consumption, acid–base balance and concentrations of sodium, potassium, glucose, lactate and calcium. Concentrations of sodium and potassium will also be measured in the urine at the end of EVNP.

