### Renal fibrosis

One of the most common causes of graft failure after transplantation is the development of chronic allograft nephropathy.^20^ The aim of this study is to determine if EVNP can slow the progression of fibrosis. Biopsies of the kidney will be taken pretransplant and after 3 months. Biopsies will be fixed in formalin and paraffin embedded cut sections of the graft will be stained with sirius red (stains for collagen III). The degree of fibrosis will be quantified using computerised digital image analysis.

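### The plan blinds no one, but its stated reason covers only the surgical team; biopsy readers and laboratory analysts could be masked at almost no cost

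*Protocol article*

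**What the plan says.** The Study type section calls the trial open-label. The Randomisation section goes further. It states that "no one is blinded to treatment allocation", and the only reason offered there is the general character of the trial.

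The strengths and limitations box at the front of the article is more specific. It says "The limitation of this study is the lack of blinding". It then offers two grounds, the technique itself and the need for safety reporting, and concludes that "it is not possible to blind the surgical team to the allocation of the kidney". No other group is named. The same box says that delayed graft function (DGF), "defined as dialysis within the first week of transplantation, is subjective", while defending it as the accepted measure.

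The outcomes that someone has to read or measure away from the bedside are these:

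- Secondary outcome measures lists "rates of biopsy-proven acute rejection rate".
- Renal fibrosis plans biopsies before transplant and at 3 months: "The degree of fibrosis will be quantified using computerised digital image analysis".
- Injury markers plans light microscopy and RNA sequencing on further biopsies, partly to establish acute tubular injury, and cytokine and injury-marker measurements in blood and urine.

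Sample storage and Data handling both say that samples are coded. Neither says that coding is meant to hide the arm.

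**The concern.** The statement that nobody is blinded is wider than the reason given for it. The reason concerns the team that handles the kidney. Pathologists, image analysts and assay staff do not handle it, and the article gives no reason of its own for letting them know the arm.

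A reader who knows the allocation may, without intending to, grade a borderline biopsy in the expected direction. There is an expectation to act on: Sample size determination reports pilot DGF of 1/18 (6%) with EVNP against 17/47 (36%) with cold storage. At stake is the credibility of the reader-assessed secondary comparisons, above all rejection, which Secondary outcomes compares between arms with Fisher's exact test and Safety outcomes also summarises by arm.

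**Working it through.** No figure in the plan bears directly on blinding, so the main check sets the passages side by side.

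**Step 1. Who must know the arm?** Perfusion takes place in a chamber outside the body. Under Postperfusion the kidney is flushed and returned to ice. Under Transplantation it is then implanted by standard techniques. The surgical and perfusion team necessarily knows the arm. Treating staff may be hard to mask. Nothing described after implantation requires a biopsy reader or laboratory analyst to know it.

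**Step 2. Which outcomes would masking reach?**

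| Outcome | What determines it | Would masking readers and analysts help? |
|---|---|---|
| DGF, duration of DGF | Dialysis decision by treating clinicians | No |
| Length of stay | Discharge decision | No |
| Biopsy-proven rejection | Decision to biopsy, then the reading | Yes, for the reading |
| Acute tubular injury by light microscopy | Reader's grade, if done by eye (the article does not say) | Yes |
| Fibrosis | Computerised image analysis | Little; exposure is already low |
| Cytokines, injury markers | Laboratory measurement | Little; exposure is already low |
| Creatinine, eGFR, CRR2, CRR5, death | Measurement or fact | Little |

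Perfusate and urine samples taken during EVNP, and the EVNP score, exist in one arm only. Masking has no meaning for them, and they enter no comparison between arms.

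**Step 3. Does sample coding already mask?** Sample storage links coding to donor-identifiable material and data protection. Data handling gives each sample a unique number. Coding would make masking easy, but the Randomisation section says outright that nobody is masked.

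**Step 4. What a shift in recorded DGF would do (illustration only).** Inputs from Sample size determination: 376 evaluable patients, control DGF 50%, α = 0.05, taken as two-sided. The 376 is close to the continuity-corrected two-proportion formula (183 per arm, 366 in total, within 3%), and 376/0.94 = 400. Per arm, n = 376/2 = 188.

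Assume no true effect and that knowledge of allocation lowers recorded DGF in the EVNP arm by b, so p2 = 0.5 − b. With p̄ = (0.5 + p2)/2, se0 = √(2p̄(1 − p̄)/n) and se1 = √((0.25 + p2(1 − p2))/n), the chance of a significant result is

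Φ((b − 1.96·se0)/se1) + Φ((−b − 1.96·se0)/se1).

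| b (points) | Chance of a significant result |
|---|---|
| 0 | 5.0% |
| 2 | 6.7% |
| 5 | 16.3% |
| 10 | 49.6% |

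The shifts and their direction are assumptions; the documents supply neither. Step 2 shows that masking readers would not change b, so these figures do not measure any gain from the fix.

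**The case against.** The trial is openly labelled and lists lack of blinding as its limitation, so nothing is concealed. Disclosure, however, does not explain why the limitation covers people who could be masked. Safety reporting is the second half of the stated reason, but the sentence applies it to the surgical team, and a pathologist can report a biopsy without knowing the arm.

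Samples are coded, and nothing says that the arm appears on tubes or request forms. That is fair: the documents do not show that analysts will see the allocation. They do state that nobody is blinded, so the protection cannot be assumed.

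A reader might infer that the bias in the primary outcome is avoidable, since the article itself calls DGF subjective, and might add that early discharge also feeds it, because Analysis population and missing data counts a patient discharged before day 7 and known to be alive at day 7 as free of DGF. The documents do not support calling this avoidable. Dialysis and discharge are decided by treating clinicians, and masking pathologists, analysts or recipients does not reach them. No listed outcome is patient-reported, so masking recipients gains little. Recording reasons for dialysis would rely on the same unblinded staff and would miss sessions not given. Such case-report-form and sensitivity-analysis detail may in any case sit in the full protocol or the statistical analysis plan, so its absence from an article is no fault.

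A reader might also infer that fibrosis is a matter of opinion. The Renal fibrosis section says otherwise. Masking its analysts is a costless precaution, not the heart of the point.

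**Conclusion.** The point holds, and it is minor. The blanket statement under Randomisation exceeds its justification and leaves reader-assessed secondary outcomes open to avoidable detection bias. These are the reading of rejection biopsies and, if graded by eye, tubular injury. Even for rejection, masking protects the reading and not the decision to biopsy, which is assumed here to rest with treating staff. No numerical size can be given from the documents.

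It would be too strong to say that a DGF difference could not be told apart from biased judgement. The plan includes creatinine-based first-week measures (functional DGF, CRR2, CRR5) and later creatinine and eGFR. Dialysis can affect early creatinine, but these measures do not rest on the dialysis decision alone and can support or contradict a DGF result. Possible bias in DGF remains a disclosed limitation.

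**What to change.** Under Randomisation, limit the open-label statement to the surgical and perfusion team and to treating staff who cannot practically be masked, so that it agrees with the strengths and limitations box. Add that:

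- pathologists reading rejection biopsies, readers of tubular injury, fibrosis image analysts and assay staff work from coded samples with allocation withheld;
- recipients are not told their allocation where feasible;
- DGF is still determined by staff who know the arm, and will be interpreted alongside functional DGF, CRR2 and CRR5.

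The cost is protocol wording and keeping allocation off biopsy and assay request forms. It needs no extra staff or procedures, leaves clinical care untouched, and keeps the sample size at 376 evaluable and 400 recruited. Masking of recipients may be imperfect.

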### Multiple vessels

DCD kidneys with multiple renal arteries will not be excluded from the trial as EVNP is technically possible in such kidneys. A cannula that preserves the carrel patch or a graft reconstruction using donor vessels will be used where possible. Nonetheless, EVNP may prove to be very difficult in kidneys with particularly complex vascular anatomy. If such a kidney is randomised to EVNP, then the local investigator may decide to use CS alone. Nonetheless, the recipient will be analysed in the EVNP arm of the study in line with the intention-to-treat basis. As per protocol, analysis will also be performed to assess the effects of the actual preservation method.

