#### Analysis population and principles

The population used for efficacy analyses will be an intent-to-treat population including all eligible randomised patients. This will be the primary analysis for the trial. Characteristics of all randomised patients will be tabulated by arm of the trial to describe the cohort.

The primary and secondary outcomes will also be analysed per protocol.

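### The supplementary per-protocol or actual-method analysis depends on a switch open only to the EVNP arm, so randomisation does not protect it

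*Protocol article*

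**What the plan says.** The section Multiple vessels states that "DCD kidneys with multiple renal arteries will not be excluded from the trial". It then makes an exception for very complex anatomy: when a kidney of this kind is allocated to EVNP, "the local investigator may decide to use CS alone". For the main analysis such a case stays where it was randomised: "the recipient will be analysed in the EVNP arm of the study in line with the intention-to-treat basis". The section closes with a further commitment: "As per protocol, analysis will also be performed to assess the effects of the actual preservation method".

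The section Analysis population and principles says of the intention-to-treat (ITT) population, "This will be the primary analysis for the trial", and adds: "The primary and secondary outcomes will also be analysed per protocol".

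The section Randomisation states that nobody is blinded. The section Primary analysis adjusts for cold ischaemic time and donor age; vascular anatomy is not a covariate.

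**The concern.** The permission to switch works in one direction only. A kidney whose vessels make EVNP impractical can leave its allocated treatment if it was allocated to EVNP. An identical kidney allocated to CS receives CS, complies with the protocol and stays in its group. The decision is made after randomisation, at the local investigator's discretion, with the allocation known.

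Any analysis that conditions on the treatment actually given therefore compares groups with different case mix. If switched kidneys are dropped, the EVNP group loses its complex kidneys while the CS group keeps its own. If they are moved, the CS group holds the complex kidneys from both arms. The covariates named for the primary model would not correct this.

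What is at stake is the result printed beside the ITT estimate. A per-protocol figure that differs from ITT could be read as the effect of EVNP when it was properly given, although part or all of the difference could come from anatomy.

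**Working it through.** **Inputs from the protocol article.** DGF is 50% in DCD transplants and the target is 35%, a 30% relative reduction (0.30 × 50 = 15 points). There are 200 patients per arm. The article gives no figure for how many kidneys would be switched or for their DGF risk, so there is no stated figure to reproduce on this point, and both quantities are varied below.

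**Assumptions.** EVNP has no effect and DGF is 50% overall. A fraction f of kidneys is unsuitable for EVNP, and all of these are switched if allocated to EVNP. DGF among unsuitable kidneys is u. The calculation is unadjusted for covariates.

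**Formulas.**
- DGF in suitable kidneys: s = (0.5 − f·u)/(1 − f)
- ITT difference (EVNP minus CS): 0.5 − 0.5 = 0
- Switched kidneys dropped: s − 0.5
- Switched kidneys moved to CS: s − (0.5 + f·u)/(1 + f)

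**Example, f = 10% and u = 80%.** s = (0.5 − 0.08)/0.90 = 46.7%. Dropped: 46.7 − 50 = −3.3 points. Moved: the CS group becomes (0.5 + 0.08)/1.10 = 52.7%, so the difference is 46.7 − 52.7 = −6.1 points (from unrounded values).

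**Spurious difference in percentage points, dropped / moved (negative favours EVNP):**

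| Unsuitable | u = 60% | u = 70% | u = 80% |
|---|---|---|---|
| 2% | −0.2 / −0.4 | −0.4 / −0.8 | −0.6 / −1.2 |
| 5% | −0.5 / −1.0 | −1.1 / −2.0 | −1.6 / −3.0 |
| 10% | −1.1 / −2.0 | −2.2 / −4.0 | −3.3 / −6.1 |

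**Direction.** With u = 50% every entry is zero. With u = 40% and f = 10%, s = (0.5 − 0.04)/0.90 = 51.1% and the CS group with the switched kidneys is (0.5 + 0.04)/1.10 = 49.1%. The differences are then +1.1 and +2.0 points, against EVNP. In general, if d is the excess risk of unsuitable over suitable kidneys, the bias is −f·d when they are dropped and −2·f·d/(1 + f) when they are moved. Moving them nearly doubles it.

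**False-positive rate** of a nominal 5% two-sided test, normal approximation, 200 per arm:
- f = 5%, d = 20 points (69% against 49%): 5.5% dropped, 6.7% moved
- f = 10%, d = 20 points (68% against 48%): 6.8% dropped, 11.2% moved
- f = 10%, d = 30 points (77% against 47%): 9.0% dropped, 19.2% moved

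**The case against.** A reader might infer that these analyses must favour EVNP even when it does nothing. The article does not support that. It describes complex vessels as an obstacle to perfusion and nowhere says that such kidneys do worse after transplantation. The direction depends on an assumption about risk, and the calculation shows zero or reversed bias without it.

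A reader might also infer that there are two separate flawed analyses, one of them as-treated. The closing sentence of Multiple vessels may simply be another description of the per-protocol analysis named later. The article does not say whether switched kidneys are dropped or moved, so the larger figures rest on one possible reading.

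The size may be small. The article regards EVNP as feasible with multiple arteries and reserves the switch for extreme anatomy, so 10% is not obviously a central value. At 2% the bias is at most 0.6 points if dropped and 1.2 if moved.

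Finally, the exact membership of a per-protocol set belongs in the statistical analysis plan, which the article says is still to be written in full, and the ITT analysis is already primary. Both statements are correct, and the absence of a detailed definition is not criticised here. What stands is that the one-sided switch and the commitment to an analysis that depends on it are both fixed in the article. A comparison built on them is not randomised, whichever way the bias runs.

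**Conclusion.** The point holds in limited form. The supplementary comparison is open to selection by vascular anatomy, in one arm only and with allocation known. Under no true effect, 50% DGF overall, 2–10% unsuitable and 60–80% DGF in those kidneys, it would show a spurious advantage for EVNP of about 0.2–3.3 points (dropped) or 0.4–6.1 points (moved). The upper ends are 3.3/15 = 22% and 6.1/15 = about 40% of the design effect. These ranges rest on assumed inputs that the article does not supply, and on complex anatomy raising DGF risk, which is plausible but not stated.

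It would be wrong to conclude that the trial's main result is at risk. Switched recipients remain in the EVNP arm under ITT, where the expected difference is zero in every scenario above. The matter is worth correcting because these results are planned for the primary and secondary outcomes and will be read beside ITT.

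**What to change.** Keep ITT as the primary analysis. The change concerns analysis only, not which kidneys are perfused.

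1. **For DGF, use a complier-average causal effect with randomisation as the instrument.** The article gives no route from CS to EVNP, so on the risk-difference scale this is essentially the ITT difference divided by the proportion of the EVNP arm actually perfused. With no true effect it is 0/(1 − f) = 0, so the case-mix bias disappears. It needs no new data. The costs are a wider confidence interval, by roughly 1/0.95 = 1.05 at 5% switched and 1/0.90 = 1.11 at 10%, and an exclusion restriction: allocation to EVNP must not itself affect DGF in kidneys that are not perfused. That assumption should be stated, since the trial is open-label and the article itself calls dialysis-defined DGF subjective.

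2. **Alternatively, make the per-protocol set symmetric.** Record for every kidney, before randomisation, whether its vessels are judged suitable for EVNP, and restrict the set to suitable kidneys in both arms. The kidney is already at the transplanting centre at that point. The cost is one case-report-form item and, at 2–10% unsuitable, 4 to 20 of 200 kidneys per arm left out of that set. This works only as far as suitability can be judged then; some difficulty may emerge only when cannulation is attempted.

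3. **In either case,** do not move switched kidneys into the CS group, say whether one or two supplementary analyses are meant, and label any remaining per-protocol results on secondary outcomes as supportive only. Extending the complier estimate to the log-rank and repeated-measures comparisons would need additional methods and is not asked for.
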